Habit is defined as a psychological construct that is dependent on associations forming between consistent contextual cues and repeated behaviors [40,41,42]. A key feature of habitual actions is that they require less cognitive processing in comparison to intentional behaviors, making the behavior more accessible to perform [43,44]. Research on habit development suggests that it can take anywhere between 18 to 254 days for a behavior to become habitual, dependent on behavioral complexity [45,46]. Physical activity is considered a complex behavior as it requires numerous choices and conducive environmental factors for the behavior to be performed, rendering it more intentional [46,47,48]. For example, to perform physical activity, choices around clothing, transport, and timing need to be considered, along with favorable environmental factors such as the weather; in comparison to simple behaviors such as taking the stairs rather than an escalator when the opportunity presents itself. By focusing on forming habitual responses to cues within the environment that promote physical movement (i.e., stairs), one can increase the amount of movement performed during the day, thus limiting sedentary behavior without taxing cognitive load [49]. Furthermore, as simple behaviors are more conducive to habit formation, they also require less time to reach habit plateau [46]. This suggests that interventions looking to utilize habit formation towards simple behaviors should highlight the measurement of habit development during the early stages of the intervention [46]. As time constraints are often an influencing factor for attrition in physical activity interventions, this structure offers a unique method to counter this barrier [19,22,50].

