### 3.2. Sample Size

To test intervention effects, there is an intended recruitment of 226 participants. Based on previous research in this field and ongoing research within this population group [56], it is anticipated that there will be approximately a 25% attrition over the four weeks of follow-up for reasons such as changes in job status, vacancy, and failure to complete questionnaires. A total sample of approximately 180 completing participants (90/group) is required to detect a medium effect in habit development towards physical movement. This sample was calculated by a power analysis using WebPower program [57]. Significance level (alpha) was established at 0.05 to avoid a Type 1 error and effect size was determined at f = 0.35. This means that for a 95% chance of detecting a significant intervention effect at a four-week follow-up, approximately 90 participants are needed in each group.

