## 4. Data Analyses

To assess the effect of the intervention on reducing occupational sedentary behavior and increasing occupational physical movement; as well as the interventions effect on increasing occupational physical movement habit and its effects on decreasing occupational sedentary behavior habit, four mixed methods 2 (condition/group) × 3 (time) ANOVA’s will be conducted. To assess the overall effects of the intervention, group (control or intervention) will be used as the between-subjects independent variable; time (baseline/T1, T2 and T3) will be used as the within-subjects independent variable with occupational sedentary behavior, occupational physical movement, occupational physical movement habit, and occupational sedentary behavior habit as the dependent variables. Each ANOVA will use an adjusted alpha level of 0.0125 to protect from inflation of type I error. Results, however, will report on any effects using the conventionally accepted significance cut-off level of 0.05 as well as the pre-specified cut-off level of 0.0125. Where an ANOVA indicates a significant time*group interaction for either of the dependent variables, a simple effects analysis will be conducted.

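### The test fixed in section 4 is a 2-df group-by-time interaction with baseline as an outcome level: valid for the course hypotheses, but inefficient and not specific to the four-week effect named in section 3.2

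*Protocol article*

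**What the plan says.** Section 4 (Data Analyses) plans four mixed ANOVAs, one per outcome, with group as the between-subjects factor and time as the within-subjects factor. Time has three levels: T1 (baseline), T2 (two weeks) and T3 (four weeks). On alpha: "Each ANOVA will use an adjusted alpha level of 0.0125 to protect from inflation of type I error"; results at 0.05 are also to be reported. The follow-up rule is: "Where an ANOVA indicates a significant time*group interaction for either of the dependent variables, a simple effects analysis will be conducted". The text does not say which simple effects are meant.

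Section 2 places randomisation after the baseline data are collected.

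Section 3.2 (Sample Size) describes the target as a "95% chance of detecting a significant intervention effect at a four-week follow-up", with these inputs: "Significance level (alpha) was established at 0.05 to avoid a Type 1 error" and "effect size was determined at f = 0.35". It concludes: "A total sample of approximately 180 completing participants (90/group) is required to detect a medium effect in habit development towards physical movement". The program used is named, but not the type of test entered into it.

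The Introduction words H1 and H2 as change across T1, T2 and T3 relative to control, not as a difference at T3 alone.

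**The concern.** Section 3.2 promises an answer about four weeks. The test in section 4 answers a broader question: whether the group difference varies in any way over T1, T2 and T3. This has three consequences.

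- **Specificity.** A difference present at T2 and gone by T3 makes the interaction significant as readily as a sustained one. A significant result is therefore not evidence of a four-week benefit. The test also has no direction, whereas the hypotheses do.
- **Gate.** Simple effects are opened only by a significant interaction, so a real T3 difference can go unexamined.
- **Efficiency.** T1 is measured before randomisation and cannot carry a treatment effect. Using it as an outcome level instead of a covariate gives up precision that the collected data would provide at no cost.

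At stake are power at the strict alpha and the risk that an early, transient difference is read as the four-week result.

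**Working it through.** **The plan's own figure.** With f = 0.35, power 95% and noncentrality f²N, the required total at alpha 0.05 is 108 for a 1-df between-group test and 128 for the 2-df interaction under sphericity. At alpha 0.0125 the totals are 143 and 165. The stated 180 follows from none of these, so it does not reveal which test was powered.

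**Inputs from the article.** N = 180 completers (90 per group), alpha 0.0125 per outcome, f = 0.35 (d = 2f = 0.70 if read as a two-group difference).

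**Assumed, because the article gives no figure.** SD 1, compound symmetry, correlation ρ of 0.3, 0.5 or 0.7, and the profile of group differences over T1, T2, T3. The value d = 0.5 is also an assumption, chosen to show an effect smaller than 0.70.

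**Formulas (noncentral F).**
- Interaction: λ = (N/4) Σ(δₜ − δ̄)² / (1 − ρ), df 2 and 2(N − 2).
- Baseline-adjusted T3 contrast: λ = (N/4) d² / (1 − ρ²), df 1 and N − 3.
- Unadjusted T3 comparison: λ = (N/4) d², df 1 and N − 2.

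**Example, profile (0, 0.25, 0.50), ρ = 0.5.** The mean difference is 0.25 and the squared deviations sum to 0.125.
- Interaction: λ = 45 × 0.125 / 0.5 = 11.25, power 70%.
- Adjusted T3: λ = 45 × 0.25 / 0.75 = 15.0, power 91%.

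**Power at alpha 0.0125, N = 180:**

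| Differences at T1, T2, T3 | ρ | Interaction | Adjusted T3 |
|---|---|---|---|
| 0, 0.25, 0.50 | 0.3 | 51% | 84% |
| 0, 0.25, 0.50 | 0.5 | 70% | 91% |
| 0, 0.25, 0.50 | 0.7 | 93% | 98% |
| 0, 0.50, 0.50 | 0.5 | 85% | 91% |
| 0, 0.35, 0.70 | 0.3 | 87% | 99% |
| 0, 0.35, 0.70 | 0.5 | 96.7% | 99.8% |
| 0, 0.70, 0.70 | 0.5 | 99.5% | 99.8% |
| 0, 0.50, 0.40 | 0.3 | 58% | 61% |
| 0, 0.50, 0.40 | 0.5 | 77% | 72% |
| 0, 0.50, 0.25 | 0.5 | 70% | 28% |

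The article's recruitment target of 226 with 25% attrition leaves 226 × 0.75 ≈ 170. At N = 170 the example gives 67% against 89%.

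**Where the gap comes from.** In the example, an unadjusted T3 comparison has 80%. About 10 points of the 21-point gap therefore come from aiming at T3 and about 11 from baseline adjustment. Adjustment helps even if T2 and T3 are tested jointly. With T1 as covariate, the residual variances at T2 and T3 are 1 − ρ² = 0.75 and the covariance is ρ − ρ² = 0.25. Then λ = 45 × 0.34375 = 15.47 on 2 and N − 4 df, and power is 86% against 70%.

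**Specificity.** For (0, d, d), (0, d, 0) and (0, 0, d) the squared deviations all sum to 2d²/3, so the interaction cannot tell them apart. At d = 0.5 and ρ = 0.5, λ = 45 × (2/3) × 0.25 / 0.5 = 15.0 and power is 85% for each. With the T2-only profile, a simulation of 4,000 trials found a significant interaction at 0.0125 together with an adjusted T3 p-value of at least 0.05 in 81% of trials.

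**The case against.** **The interaction fits the hypotheses.** H1 and H2 concern the course over three time points relative to control, and a group-by-time interaction tests exactly that. On this reading, a T2 difference is part of what was hypothesised. This stands: the planned test is valid, and baseline as a repeated level does not bias it under randomisation. What remains is that section 3.2 names four weeks and section 4 contains no test specific to that time.

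**The four-week effect may not be what was powered.** A reader might infer that the sample size was computed for a T3 group difference and then mismatched to the analysis. The article does not support that. The test type is not given, and 180 does not follow from such a test with the stated inputs. Only the wording of section 3.2 points to four weeks.

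**The power loss is not general.** This also stands. At d = 0.70 the loss is a few points at ρ = 0.5 and negligible at ρ = 0.7. Against an unadjusted T3 comparison, the interaction is ahead for a full effect at both times (85% against 80% at d = 0.5, ρ = 0.5). It also beats the adjusted T3 contrast when the effect fades enough. A claim that the interaction is always inferior would be wrong.

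**T2 might seem too early for habit.** The Introduction says "it can take anywhere between 18 to 254 days for a behavior to become habitual", and T2 falls on day 14, so a reader might infer that T2 only dilutes the habit tests. The documents do not support this. The same section says simple behaviours reach their plateau sooner and recommends measuring habit early. The 18 days are a time to becoming habitual, not to a first rise in automaticity. Two of the four outcomes are behaviours, not habits.

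**Simple effects could show T3.** A group comparison at T3 is an ordinary simple effect. Because section 4 does not specify which are run, nothing can be concluded about what they compare or whether they adjust for baseline. Even so, any such comparison remains conditional on the gate.

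**Conclusion.** The point holds as a matter of efficiency and specificity, not as an invalid analysis. The planned interaction tests the course hypotheses correctly, but it underuses baseline, can be significant from a T2-only difference, and blocks the four-week comparison when it is not significant.

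The size depends on assumptions that the article does not supply. Under compound symmetry with ρ = 0.5 and 0.5 SD at T3, the shortfall against a baseline-adjusted T3 contrast is about 21 points if half the effect is present at T2, and about 6 points if all of it is. At the protocol's f = 0.35, read as d = 0.70, it is about 3 points or less at ρ = 0.5 and about 12 points at ρ = 0.3 with half the effect at T2. The direction can reverse if the effect peaks at T2. The change is worth making because it is free and because the specificity problem does not depend on the power figures.

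**What to change.** For each outcome:

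1. Model T2 and T3 as the outcomes, with the outcome's own T1 value as a covariate and not as a time level.
2. Name the baseline-adjusted group difference at T3, with estimate and confidence interval, as the decision test at 0.0125. Do not make it conditional on the interaction or any other overall test.
3. Report the T2 difference and the overall group-by-time test (in this model, the joint test of the T2 and T3 differences) as supportive evidence for the course hypotheses.
4. Add a sentence linking the four-week target in section 3.2 to this contrast.

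The cost is a change of analysis wording, recorded as a deviation on the trial's registration. No new data or participants are needed. The downside is lower power if the effect peaks at T2 and then fades: with differences of 0.50 and 0.25 SD at ρ = 0.5, the T3 contrast has 28% against 70% for the interaction. If the investigators regard an early effect as a success in its own right, they should say so and keep the joint baseline-adjusted test of T2 and T3 as the decision test instead, accepting that it does not by itself establish a four-week benefit.

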## 5. Expected Results

This study trials a workplace-based intervention aiming to reduce occupational sedentary behavior and increase occupational physical movement through developing habits towards increasing simple physical activity behaviors throughout the workday. To date, limited interventions have used habit formation theory to reduce sedentary behavior and promote physical movement within workplace settings [68]. This theory-driven, multi-component intervention aims to address this gap by providing simple behavioral changes to increase the level of general, opportunistic movement within a sedentary population. A successful intervention will reduce sedentary behavior by developing habitual responses to simple physical activity behaviors, lessening the cognitive demand related to complex physical activity [46]. The successful intervention will be easily translatable to the general population and may be modified to suit other highly sedentary populations.

## Figures and Tables

**Figure 1 mps-05-00094-f001:**
[figure not shown]
Flow of Participants Through the Intervention.

## Data Availability

Results will be written up and peer reviewed for publication. The study is preregistered on the Open Science Framework platform (OSF, registration number: DOI 10.17605/OSF.IO/JASTP).

## Appendix A. SPIRIT Checklist

SPIRIT 2013 Checklist: Recommended items to address in a clinical trial protocol and related documents *			
Section/item	Item No	Description	Addressed on page number
**Administrative information**			
Title	1	Descriptive title identifying the study design, population, interventions, and, if applicable, trial acronym	1
Trial registration	2a	Trial identifier and registry name. If not yet registered, name of intended registry	2
	2b	All items from the World Health Organization Trial Registration Data Set	Appendix B
Protocol version	3	Date and version identifier	1
Funding	4	Sources and types of financial, material, and other support	17
Roles and responsibilities	5a	Names, affiliations, and roles of protocol contributors	1
	5b	Name and contact information for the trial sponsor	1
	5c	Role of study sponsor and funders, if any, in study design; collection, management, analysis, and interpretation of data; writing of the report; and the decision to submit the report for publication, including whether they will have ultimate authority over any of these activities	17
	5d	Composition, roles, and responsibilities of the coordinating centre, steering committee, endpoint adjudication committee, data management team, and other individuals or groups overseeing the trial, if applicable (see Item 21a for data monitoring committee)	16
Introduction			
Background and rationale	6a	Description of research question and justification for undertaking the trial, including summary of relevant studies (published and unpublished) examining benefits and harms for each intervention	3
	6b	Explanation for choice of comparators	3
Objectives	7	Specific objectives or hypotheses	5
Trial design	8	Description of trial design including type of trial (eg, parallel group, crossover, factorial, single group), allocation ratio, and framework (eg, superiority, equivalence, noninferiority, exploratory)	6
**Methods: Participants, interventions, and outcomes**			
Study setting	9	Description of study settings (eg, community clinic, academic hospital) and list of countries where data will be collected. Reference to where list of study sites can be obtained	6
Eligibility criteria	10	Inclusion and exclusion criteria for participants. If applicable, eligibility criteria for study centres and individuals who will perform the interventions (eg, surgeons, psychotherapists)	6
Interventions	11a	Interventions for each group with sufficient detail to allow replication, including how and when they will be administered	9
	11b	Criteria for discontinuing or modifying allocated interventions for a given trial participant (eg, drug dose change in response to harms, participant request, or improving/worsening disease)	N/A
	11c	Strategies to improve adherence to intervention protocols, and any procedures for monitoring adherence (eg, drug tablet return, laboratory tests)	9
	11d	Relevant concomitant care and interventions that are permitted or prohibited during the trial	N/A
Outcomes	12	Primary, secondary, and other outcomes, including the specific measurement variable (eg, systolic blood pressure), analysis metric (eg, change from baseline, final value, time to event), method of aggregation (eg, median, proportion), and time point for each outcome. Explanation of the clinical relevance of chosen efficacy and harm outcomes is strongly recommended	7
Participant timeline	13	Time schedule of enrolment, interventions (including any run-ins and washouts), assessments, and visits for participants. A schematic diagram is highly recommended (see Figure 1)	Appendix C
Sample size	14	Estimated number of participants needed to achieve study objectives and how it was determined, including clinical and statistical assumptions supporting any sample size calculations	7
Recruitment	15	Strategies for achieving adequate participant enrolment to reach target sample size	6
**Methods: Assignment of interventions (for controlled trials)**			
Allocation:			
Sequence generation	16a	Method of generating the allocation sequence (eg, computer-generated random numbers), and list of any factors for stratification. To reduce predictability of a random sequence, details of any planned restriction (eg, blocking) should be provided in a separate document that is unavailable to those who enrol participants or assign interventions	6
Allocation concealment mechanism	16b	Mechanism of implementing the allocation sequence (eg, central telephone; sequentially numbered, opaque, sealed envelopes), describing any steps to conceal the sequence until interventions are assigned	6
Implementation	16c	Who will generate the allocation sequence, who will enrol participants, and who will assign participants to interventions	6
Blinding (masking)	17a	Who will be blinded after assignment to interventions (eg, trial participants, care providers, outcome assessors, data analysts), and how	6
	17b	If blinded, circumstances under which unblinding is permissible, and procedure for revealing a participant’s allocated intervention during the trial	N/A
**Methods: Data collection, management, and analysis**			
Data collection methods	18a	Plans for assessment and collection of outcome, baseline, and other trial data, including any related processes to promote data quality (eg, duplicate measurements, training of assessors) and a description of study instruments (eg, questionnaires, laboratory tests) along with their reliability and validity, if known. Reference to where data collection forms can be found, if not in the protocol	9
	18b	Plans to promote participant retention and complete follow-up, including list of any outcome data to be collected for participants who discontinue or deviate from intervention protocols	7
Data management	19	Plans for data entry, coding, security, and storage, including any related processes to promote data quality (eg, double data entry; range checks for data values). Reference to where details of data management procedures can be found, if not in the protocol	6
Statistical methods	20a	Statistical methods for analysing primary and secondary outcomes. Reference to where other details of the statistical analysis plan can be found, if not in the protocol	12
	20b	Methods for any additional analyses (eg, subgroup and adjusted analyses)	N/A
	20c	Definition of analysis population relating to protocol non-adherence (eg, as randomised analysis), and any statistical methods to handle missing data (eg, multiple imputation)	9
**Methods: Monitoring**			
Data monitoring	21a	Composition of data monitoring committee (DMC); summary of its role and reporting structure; statement of whether it is independent from the sponsor and competing interests; and reference to where further details about its charter can be found, if not in the protocol. Alternatively, an explanation of why a DMC is not needed	N/A
	21b	Description of any interim analyses and stopping guidelines, including who will have access to these interim results and make the final decision to terminate the trial	N/A
Harms	22	Plans for collecting, assessing, reporting, and managing solicited and spontaneously reported adverse events and other unintended effects of trial interventions or trial conduct	6
Auditing	23	Frequency and procedures for auditing trial conduct, if any, and whether the process will be independent from investigators and the sponsor	17
**Ethics and dissemination**			
Research ethics approval	24	Plans for seeking research ethics committee/institutional review board (REC/IRB) approval	6
Protocol amendments	25	Plans for communicating important protocol modifications (eg, changes to eligibility criteria, outcomes, analyses) to relevant parties (eg, investigators, REC/IRBs, trial participants, trial registries, journals, regulators)	6
Consent or assent	26a	Who will obtain informed consent or assent from potential trial participants or authorised surrogates, and how (see Item 32)	6
	26b	Additional consent provisions for collection and use of participant data and biological specimens in ancillary studies, if applicable	N/A
Confidentiality	27	How personal information about potential and enrolled participants will be collected, shared, and maintained in order to protect confidentiality before, during, and after the trial	6
Declaration of interests	28	Financial and other competing interests for principal investigators for the overall trial and each study site	17
Access to data	29	Statement of who will have access to the final trial dataset, and disclosure of contractual agreements that limit such access for investigators	6
Ancillary and post-trial care	30	Provisions, if any, for ancillary and post-trial care, and for compensation to those who suffer harm from trial participation	N/A
Dissemination policy	31a	Plans for investigators and sponsor to communicate trial results to participants, healthcare professionals, the public, and other relevant groups (eg, via publication, reporting in results databases, or other data sharing arrangements), including any publication restrictions	6
	31b	Authorship eligibility guidelines and any intended use of professional writers	13
	31c	Plans, if any, for granting public access to the full protocol, participant-level dataset, and statistical code	6
**Appendices**			
Informed consent materials	32	Model consent form and other related documentation given to participants and authorised surrogates	19
Biological specimens	33	Plans for collection, laboratory evaluation, and storage of biological specimens for genetic or molecular analysis in the current trial and for future use in ancillary studies, if applicable	N/A
* It is strongly recommended that this checklist be read in conjunction with the SPIRIT 2013 Explanation & Elaboration for important clarification on the items. Amendments to the protocol should be tracked and dated. The SPIRIT checklist is copyrighted by the SPIRIT Group under the Creative Commons “Attribution-NonCommercial-NoDerivs 3.0 Unported” license.			

